**Methods and analysis::**

This open-label single-arm prospective study will include 35 community-dwelling older women who were diagnosed with spinal sarcopenia in our previous cohort study. The 12-week combined intervention will consist of back extensor strengthening exercise and nutritional supplementation. The primary outcome of this study will be isometric back extensor strength after the 12-week intervention. All functional and radiographic outcomes will be measured at 0, 12, and 24 weeks post-intervention. The data will be analyzed using the intention-to-treat principle.

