### Background

1.1

Spinal sarcopenia is a multifactorial disorder associated with the atrophy of and fatty changes to the paraspinal muscles.^[1]^ With age, the cross-sectional area of the paraspinal muscles tends to decrease, whereas the fat infiltration increases.^[2]^ Paraspinal muscle atrophy significantly contributes to spinal disorders in terms of back pain, low quality of life (QoL), and spinal dysfunction.^[3]^ It also leads to the loss of lumbar segmental stability, resulting in recurrent low back pain.^[4]^ Spinal sarcopenia is correlated with spinal sagittal imbalance due to insufficient compensation by flattening thoracic kyphosis (TK) in patients with a spinopelvic mismatch.^[5]^

The development of new medical technologies and pharmacological treatments for sarcopenia, ranging from prevention to treatment and rehabilitation, is an immediate task in ageing societies. In particular, although the development of new drugs is urgently required for the medical access and treatment of sarcopenia, no new drug has yet passed phase III or higher clinical trial testing.^[6]^ Therefore, resistance exercise and nutritional supplementation,^[7]^ the current first-line interventions for the prevention and treatment of sarcopenia, should be applied equally in cases of spinal sarcopenia.

In a preliminary study in 2019, we recruited elderly community-dwelling individuals (SarcoSpine cohort).^[1]^ In that study, lumbar spine magnetic resonance imaging (MRI) was performed for the quantitative evaluation of the lumbar extensor muscles (LEM) of all subjects, while several functional tests of the spine, including isometric/isokinetic back muscle strength and back performance tests, were conducted. The second wave of the cohort is expected to begin in the second half of 2021. Here, we describe a planned pilot study of a combined exercise and nutrition intervention for treating spinal sarcopenia in elderly women whose spinal muscle mass is in the lower 50% of this cohort. This study will aim to determine whether completing 12 weeks of the combined intervention has a therapeutic effect on spinal sarcopenia in elderly women.

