1.*Isokinetic back muscle strength*The investigators will use an isokinetic dynamometer (Biodex Multi-Joint System; Biodex Corporation, Shirley, NY, USA) to measure the back extensor torque. Briefly, the examination will be performed by seating the patient comfortably in the device, fixing both the thighs and the back to the chair using a strap, and asking the patient to hold the handle placed near the chest for the measurement of the upper limb and hip joint motions. The dynamometer axis will be located on the anterior superior iliac spine of the patient's pelvis. All patients will be instructed to flex and extend the back 5 times at an angular velocity of 60°/sec as a warm-up before the examination. During the examination, the patients will be instructed to execute maximal-effort back flexion and extension 10 times at an angular velocity of 60°/sec. The back range of movement will be limited at 50° with 30° (−30°) of trunk flexion and 20° (+20°) of trunk extension relative to the anatomical reference position (0°).^[12]^ The device will measure the peak torque (Nm) and the peak torque per body weight (Nm/kg).^[13]^2.*LEM mass*DEXA (Lunar iDXA for Bone Health; GE Healthcare, Schenectady, NY, USA) will be used to analyze LEM mass. Lateral whole-body scans will be taken according to the enCORE-based X-ray Bone Densitometer User Manual. The lateral positioner and the instructions below aim to position the lumbar spine straight and parallel to the scanner table: 1) place a pillow under the subject's head, 2) allow the subject to lie on the left side with the lower limb joint as comfortable as possible, 3) position the subject's back and hips flat against the positioner, and 4) position the subject's arms at 90° from the chest. After the lateral DEXA scan is taken, the region of interest (ROI) will be defined to analyze the LEM composition.Lumbar spine MRI will be also performed immediately after the 12-week intervention using a 1.5-T scanner (Achieva 1.5T; Philips Healthcare, Netherlands). The imaging protocol will include sagittal T2-weighted fast spin-echo imaging (repetition time, 3200 ms/echo; echo time, 100 ms; echo-train length, 20; section thickness, 4 mm; and field of view, 300 × 300 mm) and axial T2-weighted fast spin-echo imaging (repetition time, 3500 ms/echo; echo time, 100 ms; echo-train length, 20; section thickness, 4 mm; and field of view, 200 × 200 mm). Axial images (5 slices) will be obtained of each lumbar intervertebral level (T12/L1–L5/S1) parallel to the vertebral endplates. Three-dimensional segmentation of the LEM will be performed to measure the mean volume and signal intensity. The right and left LEM compartments will be separately segmented from the mid-disc level of T12/L1 to the mid-disc level of L4/5. A semi-automated random walk 3D segmentation algorithm, a magic cut tool for segmentation work of radiological software (AVIEW Research; Coreline, Seoul, South Korea) will be used to volumetrically segment the LEM.^[14]^ During the segmentation, an experienced radiologist will repeatedly modify the procedures and confirm the segmentation results. In this process, the ROI will be positioned at the muscle contour with care taken to avoid the accidental inclusion of subcutaneous fat or the muscle–fat interface. Bilateral LEM compartments will be combined to determine the mean signal intensity and volume. The mean signal intensity of the LEM reflects the intramuscular fat content because signal intensity increases as fat content increases.3.*Conventional sarcopenic indices*A.Appendicular skeletal muscle mass (ASM): DEXA and bio-impedance analysis (InBody 720; Biospace, Seoul, South Korea) will be performed to analyze body composition, including lean body and fat masses. ASM will be calculated by summing the lean masses of the bilateral upper and lower extremities^[15]^ and standardized by being divided by the squared height value (ASM/Ht^2^ [kg/m^2^]).B.Handgrip strength: A handgrip dynamometer (T.K.K.5401; Takei Scientific Instruments, Tokyo, Japan)^[16]^ will be used to determine handgrip strength, as described previously.^[17]^ Briefly, while sitting in a straight-backed chair with their feet flat on the floor, the patients will be asked to adduct and neutrally rotate the shoulder, flex the elbow to 90°, and place the forearm in a neutral position with the wrist in 0–30° of extension and 0–15° of ulnar deviation. The subjects will be instructed to squeeze the handle as hard as possible for 3 seconds, and the maximum contraction force (kg) will be recorded.C.Performance: The Short Physical Performance Battery, which includes 3 objective physical function tests (ie, time taken to cover 4 m at a comfortable walking speed, time taken to stand from sitting in a chair 5 times without stopping, and ability to maintain balance for 10 seconds in 3 different foot positions at progressively more challenging levels), will be used to determine lower extremity function.^[18]^ A score of 0–4 will be used to grade the performance of each task, with higher scores indicating better lower extremity function.4.*Spine specific outcomes*A.Spinal sagittal balance (SSB): For each participant, 1 lateral radiograph of the whole spine will be collected and digitized. All measurements will be performed using imaging software (INFINITT PACS M6; INFINITT Healthcare, Seoul, South Korea), as previously described.^[19,20]^ Briefly, the following spinopelvic radiographic parameters will be analyzed: sacral slope (SS), pelvic incidence (PI), pelvic tilt, lumbar lordosis (LL), TK, LL to PI ratio (LL/PI), PI-LL mismatch (difference between PI and LL), and sagittal vertical axis. PI-LL will be the primary SSB outcome.^[21]^B.Mobility-related activity: The Back Performance Scale (BPS), which consists of the sock test, pick-up test, roll-up test, fingertip-to-floor test, and lift test, will be used to assess trunk mobility. These 5 tests are associated with each other and have high internal consistency, implying that they share the ability to measure physical performance.^[22]^ The BPS sum score (0–15) is calculated by adding the individual scores of the 5 tests.C.Isometric endurance of the back: The Sorensen test, which is the most widely used test in published studies to evaluate the isometric endurance of the trunk extensor muscles, will be used to measure the duration of time a person can hold the unsupported upper body in a horizontal prone position with the lower body fixed to the examining table.^[23]^5.*Other functional outcomes*A.Balance and fall risk: Each participant's balance and fall risk will be evaluated using the Berg Balance Scale (range: 0–56; lower scores indicate worse outcomes).^[24]^B.Quality of life: The Euro Quality of Life Questionnaire 5-dimensional classification (score range, 0–1; lower scores indicate worse outcomes) will be used to evaluate patients’ QoL.^[25]^C.Ability to perform activities of daily living (ADLs): The Korean version of the Modified Barthel index^[26]^ (score range, 0–100; lower scores indicate worse outcomes) and the Korean version of the Instrumental ADL (score range, 0–3; higher scores indicate worse outcomes) will be used to evaluate each subject's ability to perform ADLs.^[27]^D.Frailty: The Korean version of the FRAIL scale will be used to assess frailty using the fatigue, resistance, ambulation, illness, and loss of weight components (score range, 0–5; lower scores indicate worse outcomes).^[28]^

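### Mean T2-weighted signal is read directly as muscle fat with no reference tissue or fat-fraction step named, so scaling and fat cannot be told apart across women or sessions

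*Protocol article*

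**What the plan says.** Section 1.1 (Background) makes fat part of the disease itself: "Spinal sarcopenia is a multifactorial disorder associated with the atrophy of and fatty changes to the paraspinal muscles".

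Section 2.4 (Outcomes measures), item 2, describes the MRI measurement in detail.
- **Scanner and timing:** "Lumbar spine MRI will be also performed immediately after the 12-week intervention using a 1.5-T scanner (Achieva 1.5T; Philips Healthcare, Netherlands".
- **Sequence:** a weighted one, "axial T2-weighted fast spin-echo imaging (repetition time, 3500 ms/echo; echo time, 100 ms; echo-train length, 20; section thickness, 4 mm". No T2 map or fat-fraction sequence is named.
- **Measured quantities:** "Three-dimensional segmentation of the LEM will be performed to measure the mean volume and signal intensity".
- **Pooling of sides:** "Bilateral LEM compartments will be combined to determine the mean signal intensity and volume".
- **Interpretation:** "The mean signal intensity of the LEM reflects the intramuscular fat content because signal intensity increases as fat content increases".

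The region of interest follows the muscle outline and is drawn to keep out subcutaneous fat and the border between muscle and fat. The text does not mention dividing by the signal of another tissue, a phantom, or a fat fraction. It does not say that values are unscaled either.

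For a possible earlier scan, section 1.1 says of the 2019 cohort that "lumbar spine magnetic resonance imaging (MRI) was performed for the quantitative evaluation of the lumbar extensor muscles (LEM) of all subjects". The article does not name that scan as baseline.

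**The concern.** The stated reasoning, that more fat gives more signal, orders tissues correctly within one image. It does not make a number from one scan comparable with a number from another. T2-weighted signal is in arbitrary units. It depends on receiver gain, coil loading, body size and image scaling at each session, and it also rises with muscle water.

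A mean intensity becomes informative only when set beside another. That can be another woman's value, the same woman's cohort scan, or a further trial scan. Each of these comparisons crosses sessions.

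The companion measure has a limit of its own. If signal inside the contour reflects intramuscular fat, that fat lies inside the contour and is counted in the volume.

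At stake is the only quantity that the article expressly interprets as intramuscular fat, in a condition that it defines partly by fatty change.

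**Working it through.** The plan states no figure for this outcome, and section 2.6 bases the sample size on feasibility. There is nothing to reproduce. The numbers below only illustrate scale.

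**Inputs**
- From the article: n = 35, single arm, one named scanner (sections 2.1 and 2.4); significance level 0.05 (section 2.5), taken as two-sided.
- Assumed: scaling CV per scan c = 5%, 10% or 20%; common shift between two occasions d = 0%, 5% or 10%; true between-woman CV of 15% or 25%; no true change in fat.

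**Step 1. Why a ratio helps.** Write the observed signal as g × S, where g is the session's scale factor and S depends on the tissue. Comparing two scans gives (g2 × S2)/(g1 × S1). With S unchanged this equals g2/g1, which cannot be told from a change in fat. Dividing by a reference tissue in the same image gives (g × S_LEM)/(g × S_ref), and g cancels.

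**Step 2. Random scaling between two scans.** The SD of apparent change is c × √2. The 95% half-width for the mean change is t(0.975; 34) × SD/√35, with t = 2.032.

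| c | SD of apparent change | 95% half-width of mean |
|---|---|---|
| 5% | 7.1% | 2.4% |
| 10% | 14.1% | 4.9% |
| 20% | 28.3% | 9.7% |

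With d = 0 the false-positive rate of a paired t-test stays at 5%. Random scaling widens the interval and does not bias the mean.

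**Step 3. A shift common to all women.** The noncentrality is d × √35/SD. For d = 5% and c = 5% it is 0.05 × 5.916/0.0707 = 4.18. The noncentral t distribution with 34 degrees of freedom gives the probability of a significant result when fat has not changed.

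| c | d = 5% | d = 10% |
|---|---|---|
| 5% | 0.98 | 1.00 |
| 10% | 0.53 | 0.98 |
| 20% | 0.17 | 0.53 |

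**Step 4. Comparison between women at one visit.** The share of variance due to scaling is c²/(c² + true CV²). For c = 10% and true CV 15% this is 0.0100/(0.0100 + 0.0225) = 31%.

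| c | true CV 15% | true CV 25% |
|---|---|---|
| 5% | 10% | 4% |
| 10% | 31% | 14% |
| 20% | 64% | 39% |

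**Step 5. Volume.** Contour volume = lean volume + intramuscular fat volume. If fat replaces muscle and the outline does not move, the sum is unchanged. Fat-free volume = contour volume × (1 − fat fraction), so it needs a fat fraction. A signal ratio alone does not supply one.

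**The case against.** The strongest objection is that the problem is read out of silence. The article never calls the values raw. It cites earlier work for the secondary outcomes and for the segmentation, and normalisation may be described there. A condensed article may leave such a step out. This stands in part: the documents do not support saying that unscaled values will be analysed. However, the text is detailed down to echo-train length and pooling of sides, and it moves straight from mean signal to fat content. Asking it to state the measure is fair.

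Second, the affected comparisons are not laid out. Table 1 and section 2.4, item 2, place one trial MRI at Week 12, the cohort scan is not named as baseline, and section 2.5 describes paired comparisons over time with no between-women analysis of signal. A reader might infer that scaling shifts will be reported as fat changes. The documents do not support that: it would need a second scan in use and a shift common to all women. One scanner and one sequence also limit scaling differences during the trial, though they do not remove them. The Abstract does say "All functional and radiographic outcomes will be measured at 0, 12, and 24 weeks post-intervention". That conflict over MRI timing is a separate issue, and normalisation would not settle it.

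Third, a reader might infer that MRI is the only outcome bearing on fat. The same item also uses lateral DEXA to analyse LEM composition, so that is too strong, although the article spells out no paraspinal fat output from DEXA.

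Fourth, Table 1 puts MRI, strength testing and exercise at the Week 12 visit, and one might infer that muscle water after exertion raises the signal. No order is stated, so no error is shown.

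**Conclusion.** The point holds as a cheap improvement to a secondary outcome. As written, mean T2-weighted signal is interpreted as intramuscular fat without a named reference, so scaling could not be separated from fat in any comparison between women or sessions. Contour volume does not by itself show lean muscle.

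The size is unknown. Under the assumed scaling CVs of 5% to 20%, scaling alone gives an apparent-change SD of 7.1% to 28.3% between two scans, and 4% to 64% of the variance between women, depending on the assumed true spread. These figures rest wholly on assumptions. The documents give no evidence that a common shift occurred, and without one a mean change loses precision but is not biased. The primary outcome does not depend on MRI.

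**What to change.** On the T2 images already planned, replace mean signal intensity with one of two measures:
- the ratio of LEM signal to a reference tissue on the same slices (for example subcutaneous fat or CSF); or
- a threshold-based fat fraction inside the contour already drawn, with the threshold set relative to signal in the same image, since a fixed absolute threshold would carry the same scaling problem.

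If the cited method already normalises, say so in section 2.4. With a fat fraction, report fat-free LEM volume beside total volume. Process any cohort scan used for comparison in the same way. If none of this is done, limit the statement that signal intensity represents fat content.

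**Cost:** a small extra region per scan for the reference tissue, which the same radiologist can draw, and a few lines of protocol text. No extra imaging is needed. Values may not match earlier cohort intensities unless those are re-scaled. A reference ratio removes a common scale factor but does not remove the effect of muscle water on the signal.

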
### Data analysis

2.5

Data will be collected using a standardized data entry form and entered into the data management system. The intention-to-treat principle will be used for data analysis. Participant characteristics will be described using means and standard deviations for continuous data and frequencies and percentages for categorical data. To compare paired data between 2 different points, we will use repeated measures analysis of variance and Friedman tests for continuous and non-parametric data, respectively. Statistical significance will be defined as *P* values <.05. All statistical analyses will be performed using SPSS version 19.0 for Windows (IBM Corp., Chicago, IL, USA).

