### Trial design

2.1

This will be an open-label single-arm study of 35 community-dwelling older women in a single center (SMG-SNU Boramae Medical Center) with a 24-week follow-up period. The trial has been registered prospectively with the Clinical Trials.gov Registry (NCT04810312) prior to participant recruitment. Important protocol modifications will be communicated to the trial registry.

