### Sample size

2.6

We intended to perform the sample size calculation based on the difference in mean isometric back muscle strength or LEM mass. However, no data, let alone effect sizes, are available in the literature concerning isometric back muscle strength or LEM mass in general practices or hospitals. Therefore, we based our sample size calculation on feasibility and the number of participants in our previous cohort study.

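### The plan promises intention-to-treat, but its named tests (repeated measures ANOVA and Friedman) by default analyse only women with complete outcome data

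*Protocol article*

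**What the plan says.** The analysis principle appears twice in the protocol article. The Abstract (Methods and analysis) says "The data will be analyzed using the intention-to-treat principle", and section 2.5 (Data analysis) says "The intention-to-treat principle will be used for data analysis". Section 2.5 then fixes the tests: "To compare paired data between 2 different points, we will use repeated measures analysis of variance and Friedman tests", the first for continuous and the second for non-parametric data. It also fixes the software: "All statistical analyses will be performed using SPSS version 19.0 for Windows".

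The primary outcome is isometric back extensor strength after the 12-week intervention (Abstract). Table 1 in section 2.4 places strength testing at three visits only: screening (Visit 0), Week 12 (Visit 7) and Week 24 (Visit 8). The visits from Week 0 to Week 10 carry exercise education and supplements but no outcome measurement.

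On design, section 2.1 says: "This will be an open-label single-arm study of 35 community-dwelling older women in a single center". On size, section 2.6 says: "Therefore, we based our sample size calculation on feasibility and the number of participants in our previous cohort study". The article gives no effect size, SD, power or expected dropout.

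**The concern.** A single-arm study has no randomised allocation to preserve. Intention-to-treat can then only mean that every enrolled woman stays in the analysis. Repeated measures ANOVA and the Friedman test both need a full row of values per participant and, by default, remove anyone with a gap in the occasions entered. The named method therefore does not by itself deliver the named principle.

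Two things are at stake. First, valid Week 12 data may be discarded because of a missing Week 24 value, from a sample of only 35. Second, there is no control arm to absorb selective loss. If women who gained least are the ones not measured, the before-after gain among those who remain is too large, and it would be reported under an intention-to-treat label.

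**Working it through.** The plan states no power or dropout figure, so there is nothing to reproduce. The check sets out what the named tests do, then sizes the loss under stated assumptions.

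**Inputs from the article.** N = 35, single arm (2.1); significance level 0.05 (2.5), taken as two-sided because sidedness is not stated; strength measured at baseline, Week 12 and Week 24 (Table 1); primary time point Week 12 (Abstract).

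**Assumed inputs.** Loss by Week 12 / by Week 24 of 5%/10%, 10%/20% or 15%/30%, with women who leave not returning.

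**Step 1: who is kept.** With two occasions, n = 35 × (1 − loss by Week 12). With three occasions, n = 35 × (1 − loss by Week 24).

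| Loss by Week 12 / Week 24 | Two occasions | Three occasions |
|---|---|---|
| 5% / 10% | 33.2 | 31.5 |
| 10% / 20% | 31.5 | 28.0 |
| 15% / 30% | 29.8 | 24.5 |

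In the middle row, the three-occasion model discards 31.5 − 28.0 = 3.5 women who have a usable primary endpoint.

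**Step 2: the two-occasion case.** A two-level repeated measures ANOVA is the paired t-test. On a simulated data set of 35 pairs, F and t² were both 1.3906. Week 24 then plays no part, but a woman without a Week 12 value is still removed.

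**Step 3: power.** Paired t-test with n − 1 degrees of freedom and noncentrality 0.5 × √n for a change of 0.5 SD (SD of the change):

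| n | 0.5 × √n | Power at 0.5 SD | Change detectable with 80% power |
|---|---|---|---|
| 35 | 2.958 | 0.82 | 0.487 SD |
| 32 | 2.828 | 0.78 | 0.511 SD |
| 31 | 2.784 | 0.77 | 0.520 SD |
| 28 | 2.646 | 0.72 | 0.549 SD |

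The drop caused by the three-occasion deletion is 0.82 to 0.72 if nobody is lost before Week 12. If about 10% are already lost by then (31 or 32 women), it is 0.77–0.78 to 0.72.

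**Step 4: bias if Week 24 loss depends on the Week 12 gain.** Assume a true mean gain of 0.40 SD and a logit of missing Week 24 equal to −1.4 − 0.5 × (a woman's deviation from the mean gain). The odds of being missing then rise by exp(0.5) = 1.65 per SD smaller gain. In 20,000 simulated trials about 27.7 women are kept, and the complete-case gain is about 0.50 SD instead of 0.40 (+25%). With half that dependence (0.25 per SD) it is 0.45; with none, 0.40. This applies to the primary result only under the three-occasion reading, and there an analysis of all observed Week 12 values returns 0.40.

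**Step 5: the same loss acting before Week 12.** This applies under either reading. With an assumed baseline–Week 12 correlation of 0.7 and equal variances, the complete-case gain is again about 0.50 SD. A likelihood-based estimate using every woman's baseline gives 0.48 to 0.49 SD, so almost all the bias remains.

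In a separate simulation with no true change and 20% loss, the complete-case mean change was 0.00, +0.10 and +0.21 SD for correlations of 0, 0.3 and 0.6 between a woman's change and her tendency to stay. The type I error was 0.05, 0.08 and 0.21.

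**The case against.** The strongest reply is that section 2.5 speaks of comparing two points and the primary outcome is at Week 12. Read literally, the primary test is baseline against Week 12, and a missing Week 24 value costs nothing. This stands as a possible reading. The other reading is also open, because these tests are normally chosen for three or more occasions and the study has three. The ambiguity changes how many women are lost. It does not change the fact that incomplete cases are removed.

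A second reply is that this is a condensed article, and imputation before the ANOVA would be compatible with both statements. That is fair: the absence of an imputation rule here is not a finding, and a complete-case result is the default rather than a certainty. What remains is that the article itself fixes principle, tests and software, and the tests do not give what the principle promises.

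Third, a mixed model does little for women who leave before Week 12 because they gained little. Step 5 confirms this, and it limits what the fix can claim.

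Three stronger inferences are tempting, and the article does not support them:

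- A reader might infer that missing any visit removes a woman. Table 1 shows that only three visits carry strength, so a missed training visit removes nobody.
- A reader might infer that a missing Week 24 value certainly removes her from the Week 12 result. That needs three occasions in one model, which the text does not fix.
- A reader might take the aim in section 1.1, to "determine whether completing 12 weeks of the combined intervention has a therapeutic effect on spinal sarcopenia in elderly women", as restricting the analysis to completers. It is a Background sentence and defines no analysis set.

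**Conclusion.** The point holds in a limited form. The article promises intention-to-treat and names tests that, by default, give a complete-case analysis wherever outcome data are missing. Under the three-occasion reading, that includes discarding valid Week 12 data from women who miss Week 24. Under the two-point reading, only women missing baseline or Week 12 are lost.

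The size is not known, because it rests wholly on assumed dropout. The illustrative case of 28 women kept, with its power loss and the 25% overstatement of the gain, holds only for about 20% missing Week 24 under the three-occasion reading; the overstatement also needs the assumed dependence on gain. The power loss is not a shortfall against a target, since the plan set none and chose 35 on feasibility.

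For a small single-arm pilot this is a should-fix: the correction is cheap, and it decides what the primary result may be called.

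**What to change.** In section 2.5, replace the sentence naming the tests with wording such as:

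> Continuous outcomes will be analysed with a linear mixed model for repeated measures (SPSS MIXED, time as a categorical effect, unstructured covariance) using all observed data from every enrolled woman. The primary contrast is Week 12 minus baseline. A complete-case repeated measures ANOVA will be a sensitivity analysis.

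Add that the number of women without a Week 12 value will be reported, with a simple sensitivity analysis for them, for example assuming no change from baseline. This addition is needed because the mixed model assumes data are missing at random and does not remove bias from women who stop early because they gained little. Any outcome left to the Friedman test should be labelled complete-case, with the number analysed.

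The cost is wording and one extra analysis. The procedure is available in the SPSS version already named, and no new data or visits are needed.

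### Section 2.5 pairs a two-point comparison with tests built for three or more visits: with two visits Friedman is only a sign test, and with three a significant result does not by itself show a week-12 effect.

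*Protocol article*

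**What the plan says.** The Abstract (Methods and analysis) fixes the primary outcome and its time: "The primary outcome of this study will be isometric back extensor strength after the 12-week intervention". The same paragraph gives the measurement schedule: "All functional and radiographic outcomes will be measured at 0, 12, and 24 weeks post-intervention". Section 2.4 and Table 1 show that this means baseline, the end of the 12-week programme, and 12 weeks after that. Section 2.1 gives the design: "This will be an open-label single-arm study of 35 community-dwelling older women in a single center". Every comparison is therefore within person.

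Section 2.5 holds the only sentence on testing: "To compare paired data between 2 different points, we will use repeated measures analysis of variance and Friedman tests", and it assigns the two methods "for continuous and non-parametric data, respectively". The threshold is given as: "Statistical significance will be defined as *P* values <.05". The section names no week-12 contrast and does not say whether week 24 enters the same test.

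Section 2.6 gives no effect size or power. It says that "no data, let alone effect sizes, are available in the literature concerning isometric back muscle strength or LEM mass", and that "we based our sample size calculation on feasibility and the number of participants in our previous cohort study".

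**The concern.** The comparison and the tests named in the one sentence do not match. A paired comparison of two points is normally made with a paired t-test or a Wilcoxon signed-rank test. Repeated-measures ANOVA and Friedman are the usual choices for three or more repeated measures, and this trial has three. So a reader cannot tell whether the sponsor will compare pairs of visits or run all three visits in one test.

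The choice has consequences. A three-visit test asks whether any of the visits differ, and the declared primary question is narrower than that. A two-visit Friedman test uses only the direction of each woman's change and ignores its size, which wastes information in a study of 35 people. Several secondary outcomes in Section 2.4 are bounded or ordinal scores that could well go to the non-parametric branch: the Short Physical Performance Battery, Back Performance Scale, Berg Balance Scale, Modified Barthel index and FRAIL scale.

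**Working it through.** The protocol states no power or effect size, so there is no figure of its own to reproduce.

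**Inputs.** From the protocol: n = 35 (Section 2.1), three measurement times (Abstract, Table 1), significance level 0.05 (Section 2.5). Assumed: two-sided testing; a mean change of dz standard deviations of the change, with dz from 0.3 to 0.6; normal changes; no ties; and, for three visits, equal variances and equal correlations between visits.

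**Two visits, ANOVA branch.** With two levels, F = t² on 1 and n − 1 degrees of freedom. In a simulated data set of 35 pairs, F = 1.3906 and t² = 1.3906, with P = 0.2465 for both. The two tests are the same. At dz = 0.5 the noncentrality is 0.5 × √35 = 2.96, the critical t on 34 df is 2.03, and power is 0.82.

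**Two visits, Friedman branch.** Let p be the number of women who improve. The rank sums are n + p at follow-up and 2n − p at baseline, so

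Q = (2/n)[(n + p)² + (2n − p)²] − 9n = (2p − n)²/n,

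which is the squared sign-test statistic. In the same data set Q = 11²/35 = 3.457, equal to z². Rejection needs Q > 3.841, that is, p ≥ 24 or p ≤ 11 of 35, with an actual size of 0.041. At dz = 0.5 the chance that a woman improves is Φ(0.5) = 0.691, and the binomial probability of 24 or more is 0.61.

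Power at n = 35 (paired t and sign test exact, Wilcoxon from 3,000 simulated trials):

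| dz | Paired t (= two-level ANOVA) | Wilcoxon signed-rank | Two-level Friedman (= sign test) |
|---|---|---|---|
| 0.3 | 0.41 | 0.39 | 0.26 |
| 0.4 | 0.63 | 0.61 | 0.43 |
| 0.5 | 0.82 | 0.80 | 0.61 |
| 0.6 | 0.93 | 0.92 | 0.77 |

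The effect detectable with 80% power is dz = 0.49 for the paired t-test and 0.62 for the sign test. If only 28 to 30 women contribute, power at dz = 0.5 is 0.72 to 0.75 for paired t and 0.49 to 0.55 for the sign test, so the gap is of similar size.

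**Three visits.** With means in units of the SD of change, the omnibus F on 2 and 68 df has noncentrality λ = 2n Σ(μⱼ − μ̄)². The table gives rejection rates from 20,000 simulated trials per scenario at correlation 0.5. Correlation 0.8 gives nearly the same rates.

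| Means at weeks 0, 12, 24 | λ | Omnibus ANOVA | Three-visit Friedman | Direct week-12 contrast |
|---|---|---|---|---|
| 0, 0.5, 0.5 (gain kept) | 70 × 1/6 = 11.67 | 0.86 | 0.72 | 0.82 |
| 0, 0.5, 0.25 (half lost) | 70 × 0.125 = 8.75 | 0.74 | 0.58 | 0.82 |
| No change at week 12, shift of size 0.5 at week 24 | 70 × 1/6 = 11.67 | 0.86 | 0.72 | 0.05 |

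The first and third rows have the same λ and the same omnibus rejection rate, although week 12 has a full effect in one and none in the other. The omnibus P value cannot tell them apart.

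**The case against.** The strongest reply is that the sentence, read literally, is sound for the primary outcome. It says two points, a two-level repeated-measures ANOVA is the paired t-test, and isometric back strength is a dynamometer force that belongs to the continuous branch. This stands. A reader might infer from the mismatch that the primary question is either left untested or tested only by a weak sign test. The protocol does not support that. The sign test would reach the primary outcome only if strength were treated as non-parametric, and nothing in the text says it will be.

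A reader might also infer that the primary conclusion will rest on a three-visit omnibus P value. The protocol does not say so. Pairwise contrasts after an omnibus test are routine, and a fuller plan may specify them.

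The figures also need care. The case with no week-12 effect and a shift only at week 24 shows what an omnibus test can do; the protocol gives no reason to expect it. If the gain is kept to week 24, the omnibus ANOVA rejects slightly more often than the direct contrast (0.86 against 0.82). The sign-test comparison uses normal changes, which the plan would send to ANOVA. Ties and skew in the ordinal scales would alter the gap.

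What remains is that the sentence leaves two readings open, and the tests it names are the natural ones for the reading it does not state. Friedman on two points is also a poor choice, whatever a fuller plan adds.

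**Conclusion.** The point holds as a moderate one. On the two-visit reading, the primary outcome is tested validly, and the loss falls on outcomes analysed non-parametrically: about 61% power against about 80% for Wilcoxon at n = 35, under an assumed 0.5 SD gain and normal changes, for illustration only. On the three-visit reading, significance at the 0.05 level does not by itself establish a change at week 12. The identities (two-level ANOVA with paired t, two-level Friedman with the sign test) are exact. The power figures rest on the assumed effect sizes, two-sided testing and, for three visits, equal correlations. The two readings can give different P values for the primary outcome, so the choice should be fixed before the data are analysed.

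**What to change.** Replace the testing sentence in Section 2.5 with wording to this effect:

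- The primary analysis is the week-12 minus baseline change in isometric back muscle strength, reported as a mean with 95% CI and P value. It comes from a paired t-test (equivalently a two-level repeated-measures ANOVA) or from the week-12 contrast of a repeated-measures model.
- Two-point comparisons of clearly non-normal or ordinal outcomes use the Wilcoxon signed-rank test instead of Friedman.
- Week 24 versus baseline is a separate secondary contrast.
- Any test across all three visits describes the time profile only and does not support the primary conclusion.

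A mixed model is optional, since the paired t-test is adequate for this outcome. The cost is one paragraph of wording, with no additional data or visits.
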